### Statistical analyses

Baseline characteristics of participants will be reported by using descriptive statistics. Statistical analyses will be based on the intention-to-treat principle, and include all women recruited with BMI ≥ 24 kg/m^2^. Multiple linear regression models/Generalized linear mixed models will be used to examine the primary and secondary outcomes at 24^+ 0^−27^+ 6^ and 32^+ 0^−35^+ 6^ gestational weeks, at delivery, at 42 d, 6 m, and 12 m after delivery, and the models will be adjusted for the clustering effect and the baseline outcome values. Chi-squared tests will be used to compare conditions on the proportion of women who exceed the 2009 IOM guidelines’ weekly rate of GWG, and other dichotomous outcomes. We will also analyze whether the outcome disparities between the intervention and control groups vary by hospitals, BMI status before pregnancy, etc. All results will be considered statistically significant as two-side *P* < 0.05. Statistical analyses will be conducted by using R software 4.4.1.

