### Sample size estimation

The sample size was estimated to ensure adequate power for detecting group differences in GWG at both mid- (24^+ 0^−27^+ 6^ weeks) and late-pregnancy (32^+ 0^−35^+ 6^ weeks). The anticipated differences between the two groups were 2.19 kg [13] at 32^+ 0^−35^+ 6^ gestational weeks, and 1.19 kg at 24^+ 0^−27^+ 6^ gestational week [23], the SD of the gestational weight gain would be 4 kg and 2 kg at both mid- and late-pregnancy, respectively. The rate of attrition would be 10% in each group. We aimed to recruit a total of 200 pregnant women from 2 hospitals, with 100 women per hospital. The sample size will provide 80% power with α = 0.05 to detect a mean difference of 2.19 kg in the gestational weight gain between groups after the intervention from 10^+ 0^ to 13^+ 6^ gestational weeks to 34^+ 0^~35^+ 6^ gestational weeks.

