### Randomization

The study will obtain informed consent at the baseline clinic visit at 8^+ 0^ to 13^+ 6^ weeks’ gestation. Only those women who meet the inclusion criteria, consent and complete the baseline assessment will be randomly assigned to either intervention or control group.

The 100 participants from each hospital will be randomly allocated at a 1:1 ratio to either the intervention group or the control group by the study staff, stratified by the categorical variables of age (< 30 and ≥ 30 years), pre-pregnancy BMI (< 28 and ≥ 28 kg/m^2^), and history of delivery with randomly determined block sizes of 4. Neither the staff nor the participants will be blinded to the group assignment due to the nature of the intervention program. The process of the randomization will be supervised by another study staff and recorded in a Microsoft EXCEL database.

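### The stated model adjustment names none of the three patient-level factors used to stratify randomisation and does not say what the cluster is; the cost is a conservative test and, for the main target difference, about one point of power

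*Protocol article*

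**What the plan says.** **Design (Protocol article, Randomization).** In each hospital, 100 women are "randomly allocated at a 1:1 ratio to either the intervention group or the control group". Allocation is "stratified by the categorical variables of age" (under 30, or 30 and over), pre-pregnancy BMI (under 28, or 28 and over) and "history of delivery with randomly determined block sizes of 4". The unit of randomisation is the woman, and allocation takes place within hospital.

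**Analysis (Protocol article, Statistical analyses).** "Multiple linear regression models/Generalized linear mixed models will be used to examine the primary and secondary outcomes" at visits from mid-pregnancy to 12 months after delivery, and "the models will be adjusted for the clustering effect and the baseline outcome values". Age group and delivery history are not mentioned. BMI status and hospital appear only in the sentence on whether effects vary between subgroups. For dichotomous outcomes, "Chi-squared tests will be used to compare conditions on the proportion of women who exceed" the weekly-gain guideline and on other yes/no outcomes, with no adjustment mentioned.

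**Size (Protocol article, Sample size estimation).** "We aimed to recruit a total of 200 pregnant women from 2 hospitals, with 100 women per hospital".

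**The concern.** Stratified blocks balance the arms on the stratifying factors. If those factors predict weight gain, the treatment estimate varies less than it would under simple randomisation. A model without them leaves their variance in the residual, so it reports a standard error that is too large. The test is then conservative and part of the gain from stratifying is lost.

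The article gives some reason to expect that BMI group matters. Its Table 1 recommends different gains for overweight and obese women, and its Study design section says that one hospital offers an extra nutrition consultation at a BMI of 28 or more.

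The clustering term is a separate difficulty. In an individually randomised trial it could mean hospital, repeated visits within a woman, or the two project members who deliver the sessions. These lead to different models, and two analysts could implement the sentence differently.

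**Working it through.** **1. Inputs.** From the article: 200 women, 100 per arm, 10% attrition (so 90 per arm analysed), two-sided alpha 0.05, differences of 2.19 kg (late pregnancy) and 1.19 kg (mid-pregnancy), SDs of 4 kg and 2 kg. Assumed, because the article gives no figure: the strata explain R² = 0.1, 0.2 or 0.3 of the variance in weight gain.

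**2. The plan's own figure.** The article claims 80% power for 2.19 kg. With SD 4 and 90 per arm, a two-sample t calculation gives 95.7% (97.2% with 100 per arm), so the 80% is not reproduced. The wording also attaches SD 4 to mid-pregnancy and SD 2 to late pregnancy, the reverse of the order in which it lists the two differences. Both are separate matters. They are relevant here only because the power cost depends on which SD goes with which difference.

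**3. Standard errors.** The model without strata reports SE = SD × √(2/n) = 4 × √(2/90) = 0.596. With perfect balance on the strata, the true SE is 0.596 × √(1 − R²): 0.566, 0.533 and 0.499 for R² = 0.1, 0.2 and 0.3.

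**4. Type I error with strata omitted.** This is 2 × [1 − Φ(1.96/√(1 − R²))]. A simulation of the design (two hospitals of 100, eight strata each, blocks of 4, 10% loss, SD 4, 4,000 null runs per setting) checks it when blocks are incomplete and women are lost. It assumes BMI of 28 or more in 35% of women, even splits on age and delivery history, and hospital means that differ by 0 or 2 kg. The omitting model contains hospital only.

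| R² (assumed) | Cut-off 1.96/√(1 − R²) | Type I error, formula | Type I error, simulated |
|---|---|---|---|
| 0.1 | 2.066 | 3.9% | 3.8% |
| 0.2 | 2.191 | 2.8% | 3.4–3.5% |
| 0.3 | 2.343 | 1.9% | 2.1–2.3% |

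The simulated mean SE was 0.595–0.597, against empirical SDs of about 0.56–0.57, 0.55 and 0.52. It was too large at each of these R² values.

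**5. Strata included.** With hospital and the three strata as fixed effects, simulated type I error was 4.7–5.7%. The mean SE matched the empirical SD: 0.565 and 0.561, 0.534 and 0.539, 0.499 and 0.502.

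**6. Power, 90 per arm (normal approximation).** Omitted: Φ[(δ − 1.96 × SE reported)/SE true]. Included: Φ[δ/SE true − 1.96].

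| Difference, SD | R² = 0.1 | R² = 0.2 | R² = 0.3 |
|---|---|---|---|
| 2.19 kg, SD 4 | 96.5% → 97.2% | 97.2% → 98.4% | 98.0% → 99.2% |
| 1.19 kg, SD 2 | 98.4% → 98.8% | 98.8% → 99.4% | 99.2% → 99.8% |
| 1.19 kg, SD 4 | 51.5% → 55.7% | 51.6% → 60.7% | 51.7% → 66.5% |

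Simulation agrees for 2.19 kg at SD 4: 96.4% → 97.0% at R² = 0.1 and 97.3% → 98.5% at R² = 0.2. The third row is the literal mid-pregnancy pairing, which may be a slip in the order of the SDs.

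**7. Hospital as the cluster.** A hospital fixed effect gave the results in step 4. A random hospital intercept gave type I error of 5.5% at R² = 0 and 3.0–3.5% at R² = 0.2, with frequent convergence warnings.

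**The case against.** The strongest reply is that this is a condensed article. It does not call its adjustment list exhaustive, and the full covariate list may stand in an analysis plan that is not shown. The choice between linear and mixed models may simply follow the type of outcome. This limits the point to a request for clarification. It does not remove it, because the article does state an adjustment set and that set leaves out the design's own factors.

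A second reply is that the gap may be smaller than simulated. A baseline weight in the model would capture part of the BMI stratum. That is fair, and the simulation did not include it. The article defines weight gain as visit weight minus pre-pregnancy weight, however, so what its baseline value would be is itself unclear.

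Two stronger readings are tempting, and neither is supported:

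- **Standard errors that are too small.** A reader might infer that clustering means a robust standard error on two hospitals. That estimator with a normal cut-off gave about 29–31% type I error in simulation. With a t reference on 1 degree of freedom it gave about 5%, with power near 24%. The article names no such estimator and does not say that hospital is the cluster. Since it plans mixed models over several visits, clustering within a woman is a plausible reading.
- **A breach of intention to treat.** A reader might infer that women without a late weight are dropped. The article states no complete-case rule, and a woman with only a mid-pregnancy weight can still contribute to that primary outcome.

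**Conclusion.** The point holds in a limited form. The adjustment set does not match the stratified design, and the cluster is undefined. Omitting prognostic strata does not bias the estimate. It errs in one direction only, towards a standard error that is too large, with type I error of about 3.8% falling to 2.1% as the assumed R² rises from 0.1 to 0.3. If the strata explain nothing, there is no cost.

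The power lost is about one percentage point for 2.19 kg at SD 4 and less for 1.19 kg at SD 2. It reaches roughly 4 to 15 points only for 1.19 kg at SD 4, which depends on an SD pairing that is itself in doubt. The R² values are assumptions with no source in the article. This is a worthwhile improvement, not a threat to the trial's validity.

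**What to change.** In Statistical analyses, state that the primary weight-gain models include hospital, age group, pre-pregnancy BMI (as the randomisation group or continuous) and delivery history as fixed effects.

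Define the clustering term as the correlation between repeated measurements on the same woman. Handle hospital as a fixed effect only: it is a design factor, and two units cannot support a reliable random-effect variance or cluster-robust standard error.

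It would also help to say what the baseline value is for weight gain and to adjust the dichotomous analyses for the same factors.

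The cost is wording only. The stratifying factors have to be known before allocation, so no new data are needed. The change should be fixed before outcomes are compared between arms.

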In addition, pre-specified secondary outcomes also include changes of blood pressure, body fat percentage (%), fat free mass (kg), muscle mass (kg), attitude and knowledge, dietary intake, physical activity, sleep quality, quality of life, self-efficacy score, stage of change related to gestational weight control behavior, and incidence of depression and anxiety, which will be assessed from baseline (8^+ 0^−13^+ 6^ weeks) to midterm (24^+ 0^−27^+ 6^ weeks), and from baseline (8–14 weeks) to terminal (32^+ 0^−35^+ 6^ weeks). Incidence of postpartum weight retention, absolute/mean offspring weight, height, and head circumference will also be evaluated at 42 days, 6 months, and 12 months after delivery.

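### Dichotomous secondary outcomes get plain chi-squared tests that ignore the randomisation factors and baseline scores, and the plan does not say whether these or the adjusted models are the main analysis

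*Protocol article*

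**What the plan says.** Two consecutive sentences in Statistical analyses cover the same outcomes. The first is general: "Multiple linear regression models/Generalized linear mixed models will be used to examine the primary and secondary outcomes" at each time point from mid-pregnancy to 12 months after delivery, and "the models will be adjusted for the clustering effect and the baseline outcome values". The second is specific: "Chi-squared tests will be used to compare conditions on the proportion of women who exceed the 2009 IOM" weekly rate, "and other dichotomous outcomes". No stratified version of the test is mentioned.

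Under Outcomes, every dichotomous outcome is secondary: exceeding the IOM rate, GDM, preeclampsia or gestational hypertension, cesarean delivery, macrosomia, postpartum weight retention, "and incidence of depression and anxiety".

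Under Randomization: "The 100 participants from each hospital will be randomly allocated at a 1:1 ratio", and within each hospital allocation is "stratified by the categorical variables of age", pre-pregnancy BMI and history of delivery, in blocks of 4. Table 3 shows that the PHQ-9 depression score and the SAS anxiety score are taken at baseline as well as at both pregnancy follow-ups.

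**The concern.** A plain chi-squared test uses only the two-by-two table of arm by outcome. The trial balances its arms on hospital, age, BMI and delivery history, and the test then makes no use of that balance. It keeps the between-stratum variation in its error term although the design has largely removed it from the arm comparison. When the strata are prognostic, the test rejects too rarely and loses power.

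The protocol gives grounds to expect prognostic strata. The IOM threshold differs by BMI category (0.33 against 0.27 kg/week, under Outcomes). Under Study design, one hospital runs a nutrition clinic with an extra consultation at a BMI of 28 or more. For depression and anxiety, the test also sets aside baseline scores already in hand.

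The outcomes include exceeding the IOM rate and GDM, which stand closest to the trial's stated aims of preventing excessive gain and GDM. If an adjusted and a crude P value for one of them fell on opposite sides of 0.05, the article gives no rule for which one counts.

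**Working it through.** **No figure to reproduce.** The article gives no event rate, effect size or power for any dichotomous outcome. The check is therefore a reading of the text plus a simulation whose prognostic strengths are assumptions.

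**Reading.** Sentence 1 covers all secondary outcomes. Sentence 2 covers all dichotomous outcomes, each of which is secondary. Both therefore apply to the same list, and nothing ranks them.

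**Inputs from the article.** 200 women, 10% attrition, so 200 × 0.9 = 180 analysed; 1:1 allocation in blocks of 4 within hospital × age × BMI × delivery history (2 × 2 × 2 × 2 = 16 strata, taking delivery history as two levels); two-sided α = 0.05.

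**Assumed inputs.** Treatment log-odds ratio −0.85, an odds ratio of exp(−0.85) = 0.43. Intercept −0.4, so with no prognostic factors the control rate is 1/(1 + exp(0.4)) = 40% and the treated rate is 1/(1 + exp(1.25)) = 22%. The log-odds ratio per stratification factor is 0, 0.5 or 1.0; a standardised baseline score has log-odds ratio 0, 1.0 or 1.5 per SD.

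**Comparison.** Pearson chi-squared without continuity correction, against logistic regression on arm and the four stratification factors (plus the baseline score where present). There were 1,500 runs per setting.

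| Log-OR per stratification factor | Log-OR per SD of baseline score | Type I error, chi-squared / adjusted | Power, chi-squared / adjusted | Power difference (points) |
|---|---|---|---|---|
| 0 | none | 5.2% / 5.6% | 74.0% / 73.7% | −0.3 |
| 0.5 | none | 3.9% / 4.5% | 71.5% / 72.8% | 1.3 |
| 1.0 | none | 3.0% / 4.5% | 59.3% / 67.0% | 7.7 |
| 0.5 | 1.0 | 3.6% / 3.9% | 59.9% / 68.2% | 8.3 |
| 0.5 | 1.5 | 4.7% / 5.7% | 50.0% / 62.7% | 12.7 |

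Monte Carlo standard errors: √(0.05 × 0.95/1500) = 0.6 points for type I error and about √(0.7 × 0.3/1500) = 1.2 points for each power. The 1.3-point difference is therefore small against simulation noise.

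**Second simulation.** Same design, treatment odds ratio 0.45, 2,000 runs, likelihood-ratio test for the adjusted model. With stratum odds ratios of 1.6, 2.2 and 2.7, power was 71% against 74%, 66% against 71%, and 58% against 66%: losses of 3, 5 and 8 points. At 2.2 the type I error was 3.6% for chi-squared and 5.2% adjusted.

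**Event rate.** With stratum odds ratios of 2.2 and treatment odds ratio 0.45 (3,000 runs), power was about 66% against 72% at a control rate near 50%, 25% against 30% at 10%, and 14% against 20% at 5%. At 5% the adjusted likelihood-ratio test had a type I error of 5.9%, on about 180 × 0.05 = 9 events under the null.

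**The case against.** The strongest reply is that the two sentences are a general rule followed by a specific exception, so there is no contradiction. Alternatively, chi-squared may be a crude comparison beside the mixed models, and generalized linear mixed models can handle binary outcomes. Either reading is possible and the text states neither. What remains is an ambiguity about the main analysis, not a flat contradiction.

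A second reply also stands. The adjusted models name only clustering and baseline outcome values, so age, BMI category and delivery history are missing there too. Deferring to those models as written would not bring back every stratification factor.

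Third, the baseline-score argument is confined to depression and anxiety. GDM, cesarean delivery and macrosomia have no baseline value.

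A reader might also infer three stronger things that the document does not support:

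- **That only P values will be reported.** The article names a test; it does not say that estimates and intervals will be withheld, and reporting format is commonly left to the full protocol or SAP.
- **That the incidence of depression and anxiety mixes women already above the cut-off with new cases.** The article assesses incidence from baseline onward, which is compatible with counting new cases only. The risk set is not spelled out, but it is not stated wrongly.
- **That the power figures show what is lost where events are few.** They belong to common outcomes. At control rates of 5% to 10% the gain in points is similar, but both tests have little power, so the choice of test does not rescue those outcomes.

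**Conclusion.** The point holds as one of efficiency and clarity on secondary outcomes. As written, dichotomous outcomes go to a test that ignores the randomisation factors and, for depression and anxiety, the baseline scores. The article leaves open whether that test or an adjusted model is the main analysis.

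Chi-squared remains valid here. Its type I error was about 3% to 4% when only the stratification factors were prognostic and 5.2% when nothing was. There is no bias and no inflated type I error, and the primary outcomes are untouched.

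The power cost depends on prognostic strengths that the article does not give: nil with no prognostic factors, about 1 to 8 points from the stratification factors, and about 13 points with a strong baseline score. These sizes assume 180 women analysed, a treatment odds ratio of 0.43 to 0.45, a fairly common outcome and no continuity correction.

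**What to change.** Name one adjusted binary model as the main analysis for each dichotomous outcome, for example logistic regression with a standardised risk difference, or modified Poisson regression. Include arm, hospital, age stratum, BMI stratum and delivery history, and add the baseline PHQ-9 or SAS score for depression and anxiety respectively. List these covariates explicitly, because the present model sentence does not name the stratification factors.

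Where events are few, state in advance a smaller covariate set (for example hospital and BMI stratum) or a stratified Cochran-Mantel-Haenszel test. Keep the plain chi-squared test, if at all, as a supportive analysis.

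The cost is a few sentences in the analysis plan, settled before outcome data are compared by arm. All the variables are already collected.

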**Methods:**

The Healthy Gestational Weight Gain program (HGWG-pro) is a two-centered randomized controlled trial that aims to evaluate the effectiveness of a multi-component intervention on promoting appropriate gestational weight gain, preventing gestational diabetes mellitus (GDM), and improving pregnancy, delivery, and neonatal outcomes among overweight or obese pregnant women aged 18 to 40 years old in China. Two maternal and child health care hospitals will be selected from the eastern region of China. Altogether 200 women with pre-pregnancy body mass index (BMI) ranging from 24 to 40 kg/m^2^ from the two hospitals will be randomized to intervention or control group. The intervention will be delivered from 10^+ 0^-13^+ 6^ weeks’ gestation to 32^+ 0^–35^+ 6^ weeks of gestation, with biweekly counseling sessions conducted either face-to-face during routine prenatal visits or via telephone, depending on the participant’s schedule. A smartphone application and wearable smart wristband will be used to assist in providing GWG related information, monitoring dietary behaviors, physical activity and weight, and providing feedback on weight and behaviors for participants. Data will be collected at 8^+ 0^-13^+ 6^, 24^+ 0^-27^+ 6^, and 32^+ 0^-35^+ 6^ weeks’ gestation, at delivery, at 42 days, 6 months and 12 months after delivery. This study has two primary outcomes: the between-group differences in gestational weight gain at 24^+ 0^-27^+ 6^ weeks’ gestation and 32^+ 0^-35^+ 6^ weeks’ gestation. The secondary outcomes will include differences between groups in weekly rate of GWG and incidence of adverse pregnancy complications and pregnancy outcomes, changes in diet, physical activity and other offspring health indicators at follow-up visits. Metabolic blood test results including indicators such as blood sugar and blood lipids will be extracted from the electronic medical record (EMR) system, indicators such as insulin and glycated hemoglobin will be measured through the collected blood samples. This trial includes a variety of process evaluation methods to evaluate the fidelity and adherence of the intervention.

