### Outcomes

*The primary outcomes* of this study are the total GWG up to 32^+ 0^−35^+ 6^ weeks’ gestation and the GWG prior to the OGTT screening at 24^+ 0^−27^+ 6^ weeks’ gestation. Both will be calculated by subtracting the pre-pregnancy weight from the weight measured at the respective time points.

*The secondary outcomes *include rate of GWG per week. Weekly rate of GWG will be defined as GWG divided by the number of weeks between the date of LMP and the midterm survey (24^+ 0^ to 27^+ 6^ weeks’ gestation) and the terminal survey (32^+ 0^ to 35^+ 6^ weeks’ gestation). Weekly rate of GWG between study clinical visits at 8^+ 0^ weeks’ and 27^+ 6^ weeks’ gestation, and at 8^+ 0^ and 35^+ 6^ weeks’ gestation will be calculated by dividing the amount of weight gain between visits by the weeks of gestation between visits. The proportion of women who exceed the 2009 IOM guidelines’ weekly rate of GWG will also be assessed, and it was defined as being above the upper limit of the first trimester (2.0 kg) plus the upper limit of the weekly rate (0.33 kg/week for overweight with BMI ranging from 24.0 to 28.0 kg/m^2^, 0.27 kg/week for obesity with BMI ≥ 28 kg/m^2^), times the number of weeks in the second and third trimesters.

Other secondary outcomes include incidence of GDM diagnosed according to IADPSG criteria (FPG ≥ 5.1 mmol/L, and/or 1-h blood glucose ≥ 10.0 mmol/L, and/or 2-h blood glucose ≥ 8.5 mmol/L), rate of preeclampsia/gestational hypertension (preeclampsia was defined according to the criteria of the ACOG, i.e. systolic blood pressure of ≥ 140 mmHg or diastolic blood pressure of ≥ 90 mmHg occurring after 20 weeks of gestation in a previously normotensive woman combined with new-onset proteinuria of ≥ 0.3 g/24 h. Gestational hypertension was defined similarly but without the presence of proteinuria.), incidence of cesarean delivery, absolute/mean infant birth weight, incidence of macrosomia (with infant birth weight ≥ 4000 g), and absolute/mean Apgar scores at 1–5 min (Apgar scores at 1–5 min evaluate the baby’s heart rate, respiratory effort, muscle tone, reflex irritability, and color. Each category is scored from 0 to 2, and the total score ranges from 0 to 10. A higher Apgar score indicates that the newborn is in good health.).

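### Two primary outcomes are each tested at an unadjusted two-sided 0.05 with no rule for combining them; if either one suffices, the family-wise error is about 6.5–9%, not 5%

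*Protocol article*

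**What the plan says.** The Abstract (Methods) states: "This study has two primary outcomes: the between-group differences in gestational weight gain at" the mid- and late-pregnancy windows. The Outcomes section agrees: the primary outcomes "of this study are the total GWG up to" 32+0–35+6 weeks, together with the gain before glucose-tolerance screening at 24+0–27+6 weeks. It adds: "Both will be calculated by subtracting the pre-pregnancy weight from the weight measured at the respective time points".

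Statistical analyses gives one significance rule for everything: "All results will be considered statistically significant as two-side" *P* < 0.05.

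Sample size estimation says that the size was chosen for adequate power at both time points, but its closing sentence covers only the late one, with undivided alpha: "The sample size will provide 80% power with α = 0.05 to detect a mean difference of 2.19 kg". The assumed effects are given as "The anticipated differences between the two groups were 2.19 kg" at the late window and, continuing, "gestational weeks, and 1.19 kg at" the mid window. On variability: "the SD of the gestational weight gain would be 4 kg and 2 kg at both mid- and late-pregnancy, respectively".

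The article nowhere ranks the two primaries, divides alpha, adjusts for multiplicity, or says whether success means both, either, or the late one alone.

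**The concern.** With two primary tests, the error rate attached to the trial's main claim depends on how the tests are combined. The article leaves that open but fixes a flat threshold for each result. A reader applying that threshold could call the trial positive on mid-pregnancy GWG alone or on late GWG alone. The 5% used in the sample size would then not be the error rate of the primary claim. A mixed result, with one primary significant and the other not, would also have no agreed interpretation, and a rule chosen after seeing it would carry little weight.

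**Working it through.** **Inputs.** Two primary tests, each at two-sided 0.05 (Outcomes; Statistical analyses). 200 women allocated 1:1 with 10% attrition, so 100 × 0.9 = 90 evaluable per arm (Sample size estimation; Randomization). Differences of 2.19 kg late and 1.19 kg mid; SDs of 4 kg and 2 kg. The correlation ρ between the two test statistics is **not given**. It should be positive, because both outcomes subtract the same pre-pregnancy weight and the late gain contains the earlier gain. I take 0.5–0.95 as the working range and show zero as the bound.

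**1. The plan's own power figure.** Power ≈ Φ(δ / (SD·√(2/n)) − z), with z = 1.960. For 2.19 kg, SD 4 and n = 90: standard error 4 × √(2/90) = 0.596; 2.19 / 0.596 = 3.67; Φ(3.67 − 1.96) = 95.7%. With SD 2, power exceeds 99.9%. The stated 80% is therefore met only as a floor. This is a separate matter and does not affect the alpha calculation.

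**2. Family-wise error if either primary suffices.** With no true effect at either time point,

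error = 1 − P(|Z₁| < 1.96 and |Z₂| < 1.96) = 0.05 + 0.05 − P(both significant).

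| ρ (assumed) | P(both significant) | At least one false claim |
|---|---|---|
| 0 | 0.25% | 9.75% |
| 0.5 | 0.93% | 9.1% |
| 0.7 | 1.65% | 8.4% |
| 0.8 | 2.19% | 7.8% |
| 0.9 | 2.96% | 7.0% |
| 0.95 | 3.54% | 6.5% |

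The figure stays above 5% for every correlation below 1.

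**3. The same calculation if both must succeed.** The chance of a false claim is then the middle column when neither effect exists, and at most 5% when only one exists. There is no inflation.

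**4. Power under an equal alpha split (0.025 each, z = 2.241), 90 per arm.**

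- Late, 2.19 kg, SD 4: Φ(3.67 − 2.24) = 92%.
- Mid, 1.19 kg, SD 2: 1.19 / (2 × √(2/90)) = 3.99; Φ(3.99 − 2.24) = 96%.
- Mid, 1.19 kg, SD 4: 1.19 / 0.596 = 2.00; Φ(2.00 − 2.24) = 40% (51% at the full 0.05).

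The third line matters because the SD sentence, read literally, assigns 4 kg to mid-pregnancy and 2 kg to late. The effects just before it are listed late then mid, which suggests the opposite assignment. The article does not settle it.

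**5. Secondary outcomes.** The narrowest count from the Outcomes section is 4 weekly rates + 1 guideline proportion + 6 clinical or neonatal + 13 changes × 2 visits + 4 postpartum × 3 visits = 49. If no secondary effect existed, 49 × 0.05 ≈ 2.5 would be expected below 0.05. None of these tests enters the formula in step 2.

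**The case against.** The strongest reply is that the article never says that one significant primary makes a positive trial. Sizing for both time points fits a both-must-succeed rule, or two separately reported questions, at least as well. This stands: the inflation is conditional on an either-suffices reading, which the text neither states nor excludes. An aim of adequate power at both windows is not a definition of success, however, so it does not supply the missing rule.

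A second reply is that testing order and multiplicity belong in a statistical analysis plan that is not shown, and that a 0.05 threshold is compatible with a fixed sequence or with Holm-adjusted *P* values. This stands in part. A generic threshold sentence does not rule out an ordering set elsewhere. But the article is not silent: it applies the threshold to all results. A fixed sequence would have to withhold significance from the second primary when the first fails, even at *P* < 0.05, and Holm would withhold it from an unadjusted *P* of 0.03 beside a clearly non-significant partner. Either would need the published sentence to be qualified.

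A reader might also infer that the dozens of unadjusted secondary comparisons help push up the primary error, or that the error is 10%. Neither is supported. Secondary tests do not change the chance of a false primary claim, and a figure near 10% needs uncorrelated outcomes, which is implausible when both share a baseline weight. The article labels these outcomes secondary and does not say that a significant one establishes efficacy, so asking for all of them to be relabelled exploratory would be largely preference.

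**Conclusion.** The point holds for the two primary outcomes. Each is tested at an unadjusted two-sided 0.05, with no order, split or requirement that both succeed. If either suffices, the family-wise error is about 6.5–9% for assumed correlations of 0.95 down to 0.5, with a ceiling of 9.75% at zero correlation, against the 5% used in the sample size. The excess is about 1.5 to 4 percentage points. It rests on the either-suffices reading and on a correlation that the article does not give. Effect estimates and their confidence intervals are not biased by this; what is affected is the claim drawn from the two tests. The secondary outcomes are a minor matter of presentation.

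**What to change.** State the decision rule for the two primaries before outcome data are analysed by group, and limit the blanket significance sentence accordingly. Workable choices are:

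- **Fixed sequence.** Test GWG at 32+0–35+6 weeks first at two-sided 0.05, since it is the outcome in the power sentence. Test GWG at 24+0–27+6 weeks at 0.05 only if the first is significant. This holds 5% overall and costs the first test no power. The downside is that mid-pregnancy GWG cannot be claimed if late GWG fails.
- **Holm.** Compare the smaller *P* with 0.025 and, if it passes, the other with 0.05. Either outcome can then be claimed alone. At the 0.025 step, power with 90 per arm is about 92% late (SD 4) and 96% mid (SD 2), but only about 40% mid if the SDs are read literally (mid SD 4).
- **Both must succeed.** If this was the intention, say so; no alpha adjustment is needed.

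State which SD belongs to which time point, because the cost of splitting alpha depends on it. Add one sentence saying that *P* < 0.05 on a secondary outcome is not presented as confirmatory. The change amounts to a few sentences and no additional participants.
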